## Abstract

**Background::**

Mild neurocognitive disorder (mNCD) is one of the degenerative diseases that results in memory deficit, and can progress to dementia. The effectiveness of drug therapy for mNCD is still debatable, but treatment of this disease has important implications for postponing or preventing dementia. Jujadokseo-hwan (JDH) is a traditional herbal medicine formulation that exhibits improvement in cognitive abilities and neuroprotective effects. In this study, we will evaluate the safety and efficacy of JDH compared to placebo in mNCD patients.

**Methods and design::**

This is a randomized, double-blind, placebo-controlled, parallel-group, multicenter clinical trial. After obtaining informed consent from all participants and performing the screening process, the participants will be equally divided into an experimental group and a control group. Each participant will visit the trial center 7 times during the 12 weeks of intervention. The follow up study will be conducted 12 weeks after the intervention ends. The primary outcome is the variance in Seoul verbal learning test-elderly's version (SVLT-E) score from baseline to 12 weeks. Secondary outcomes include scores/values for the following variables: SVLT-E, Rey complex figure test, Digit span test, Korean-Boston naming test, calculation ability, controlled oral word association test, Korean-color word stroop test, digit symbol coding, Korean-trail making test-elderly's version, Korean version of mini mental state examination for dementia screening, euro-qol-5 dimension, pattern identifications tool for cognitive disorders, Korean version of Montreal cognitive assessment, Korean quality of life-Alzheimer disease, computerized tongue image analysis system, blood pressure pulse analyzer, bioelectrical impedance analyzer, wearable electroencephalogram device, functional near-infrared spectroscopy system, and cost analysis.

**Discussion::**

This is the first trial evaluating the efficacy of JDH for mNCD. We expect this trial will provide strong support for wide use of JDH for mNCD and lead to further research on herbal medicine treatments for mNCD.

**Trial registration number::**

KCT0003570 (Registered in Clinical Research Information Service of the Republic of Korea, https://cris.nih.go.kr/cris/search/search_result_st01.jsp?seq=12669).

## Introduction

1

Recently, degenerative diseases have a higher prevalence due to extended life expectancies. Among them, dementia has the fourth highest mortality rate after cancer, heart disease, and stroke.

Currently, mild neurocognitive disorder (mNCD) is known as a precursor for dementia.^[1]^ However, there is no apparent cure and a variety of alternative treatments are being evaluated.^[2,3]^ Various clinical studies have reported using herbal medicines to improve memory and cognition, although no well-designed randomized controlled trials have been performed so far.^[4–6]^

Jujadokseo-hwan (JDH, ZhuziDushu Wan in Chinese) is a traditional herbal medicine formulation listed in Uihak-ipmun (Yixue Rumen in Chinese). It is composed of 7 herbal components: Acori Graminei Rhizoma, Angelica Gigantis Radix, Citri Unshius Pericarpium, Ginseng Radix, Glycyrrhizae Radix et Rhizoma, Poria Sclerotium, and Poly galae Radix. In South Korea, a tablet form of JDH is approved for memory deficit (amnesia) by the Korean Ministry of Food and Drug Safety. Two experimental studies investigated the effects of JDH on the brain ability and oxidative stress and found that JDH improved brain ability, learning, and memory, and also demonstrated a neuroprotective effect.^[7,8]^

We plan to conduct a randomized, double-blind, placebo-controlled, parallel;-group, multi-central trial to evaluate the safety and efficacy of JDH in patients with mNCD.

## Methods

2

### Objectives

2.1

The main objective of this study is to evaluate the safety and efficacy of JDH compared to placebo for treating mNCD.

### Study design and setting

2.2

This study is designed as a randomized, double-blind, placebo-controlled, parallel-group, multi-center trial. The clinical trial sites are as follows: Dunsan Korean medicine Hospital of Daejeon University, Wonkwang university Sanbon hospital, and Wonkwang university oriental medical hospital, Jeonju. The anticipated number of eligible participants is 80. Subjects will be divided into 2 equal groups: the JDH group (experimental group) and the placebo group (control group). Each group will be administered JDH or placebo 3 times day for 12 weeks (84 days). After the 12-week follow-up period, participants will be instructed to visit the trial center once for safety and efficacy assessments. The primary outcome is the Seoul verbal learning test-elderly version (SVLT-E)^[9]^ score variable. The secondary outcomes include scoring variables from the SVLT-E, Rey complex figure test (RCFT),^[10]^ digit span test (DST),^[11]^ Korean-Boston naming test (K-BNT),^[12]^ calculation ability, controlled oral word association test (COWAT),^[13]^ Korea-Color word stroop test (K-CWST),^[14]^ digit symbol coding (DSC),^[15]^ Korean trail-making test-elderly's version (K-TMT-E),^[16]^ Mini-Mental state examination for dementia screening (MMSE-DS),^[17]^ EuroQol-5 Dimension (EQ-5D),^[18]^ Pattern identifications tool for cognitive disorders (PIT-C),^[19]^ Montreal cognitive assessment-Korean version (MoCA-K),^[20]^ and Korean quality of life-Alzheimer's disease (KQOL-AD) scale.^[21]^ Other secondary outcomes include measured values from computerized tongue image analysis system (CTIS, Device name: TAS-4000), blood pressure pulse analyzer (BPPA, Device name: DMP-life), bioelectrical impedance analyzer (BIA, Device name: InBody S-10), wearable electroencephalogram device (WED, Device name: neuroNicle FX2), functional near-infrared spectroscopy system (fNIRS, Device name: NS1-H20AM) and cost analysis. This protocol (version 2.1, 28 August 2018) follows the Recommendations for Interventional Trials (SPIRIT) Standard Protocol guidelines.

### Participants

2.3

#### Recruitment

2.3.1

Recruitment of the participants began in August 2018 and is expected to finish in August 2020. Recruitment may be extended depending on registration completion. All participants will be given a consent form with a full explanation before registration, and will be notified that they may be withdrawn from the trial at any point without penalty. The consent form includes information regarding background, purpose of the study, trial and placebo product, outcome, and expected benefits and harms.

#### Screening

2.3.2

Participants will be assigned a screening code (ie, DS-S-001) in the order of consent received. After the screening process, selected participants will be assigned an identification code (ie, DS-E-001). Any medication that subjects have taken 4 weeks before participating in the clinical trial may be accepted at the discretion of the researchers, if they are not prohibited drugs. If participants take these drugs during the trial, they will be discontinued from the trial or their data will be excluded from analysis.

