### Sample size calculation

2.7

Using 80% power for detecting treatment differences, a significance level of 0.05, and assuming a standardized effect difference of 0.7% and a 20% dropout rate, we conclude that a total of 80 patients is needed to ensure statistically significant results.

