### Statistical analysis

2.8

Efficacy analysis will be conducted for the intention to treat population primarily according to the full analysis set (FAS) principle and secondarily according to the per-protocol (PP) principle. Missing values will be imputed by the last-observation-carried-forward method. Safety analysis will be conducted by FAS and PP in aggregate. The statistical analysis will be performed using SPSS. *P* < .05 is considered statistically significant.

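### The rule in 2.3.2 for drug use during the trial names no analysis set and, read literally, allows post-randomisation exclusions from the ITT/FAS primary analysis

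*Protocol article*

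**What the plan says.** Section 2.3.2 (Screening) deals first with medication taken in the four weeks before entry, which "may be accepted at the discretion of the researchers, if they are not prohibited drugs". The next sentence gives the consequence of use after entry: "If participants take these drugs during the trial, they will be discontinued from the trial or their data will be excluded from analysis".

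Section 2.8 (Statistical analysis) states: "Efficacy analysis will be conducted for the intention to treat population primarily according to the full analysis set (FAS) principle". The per-protocol analysis is secondary. On missing data it says: "Missing values will be imputed by the last-observation-carried-forward method". On safety it says: "Safety analysis will be conducted by FAS and PP in aggregate".

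Section 2.4 (Study procedure) lists SVLT-E among the assessments made around randomisation, at visit 7 as part of the full battery, and at visit 8. The visit 4 list does not include it. Section 2.9.1 defines the primary endpoint as the SVLT-E change from baseline to 12 weeks.

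**The concern.** Excluding data because of something a participant does after randomisation is a per-protocol rule. Section 2.3.2 states it for analysis in general, while 2.8 puts an ITT/FAS analysis first. A later analysis plan could follow either section and claim support from the protocol.

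Three things are at stake:

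- **Who is in the primary comparison.** If the drug use is related to outcome and is more common in one arm, removing those participants leaves groups that randomisation no longer balances.
- **Discretion.** The rule offers two consequences joined by *or* and no criterion for choosing. The same participant may be left out or kept with an imputed value.
- **Which drugs trigger the rule.** *These drugs* can refer to the prohibited drugs or to the prior medication that the preceding sentence allows. On the second reading, participants would be affected for continuing medicines accepted at entry.

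Safety is also to be analysed on FAS and PP. An exclusion applied at FAS level would therefore reach the adverse-event tables as well.

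**Working it through.** **1. The plan's own figure.** Section 2.7 gives 80% power, a significance level of 0.05 (taken as two-sided), a standardised difference of 0.7 (printed with a percent sign), 20% dropout and a total of 80. With the normal approximation:

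- n per arm = 2 × ((1.960 + 0.8416)/0.7)² = 32.04
- allowing for dropout: 32.04/(1 − 0.20) = 40.05 per arm, or 80.1 in total

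This matches 80 before rounding up. The present point does not depend on it, but it supplies 40 randomised and 32 evaluable per arm for what follows.

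**2. The sections side by side.**

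| | 2.3.2 Screening | 2.8 Statistical analysis |
|---|---|---|
| Trigger | Drug use during the trial | None stated |
| Consequence | Discontinuation, or exclusion from analysis | ITT population by the FAS principle first, PP second |
| Analysis set named | No | FAS and PP |
| Cross-reference to the other section | None | None |

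No section defines the FAS with an exception for concomitant medication, and none limits the exclusion in 2.3.2 to the PP set.

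**3. Exclusion branch: simple illustration (assumed rates).** If a fraction f of an arm is removed and those participants are 1 SD worse than the rest of the arm, the arm mean improves by f × 1 SD.

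- Placebo: 4/40 = 0.100 SD
- JDH: 1/40 = 0.025 SD
- Net shift: 0.100 − 0.025 = 0.075 SD, and 0.075/0.7 = 11% of the planned difference

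With more removals from placebo, placebo looks better, so the shift runs against JDH. With the counts reversed, it favours JDH by the same amount.

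At 32 per arm the standard error is √(2/32) = 0.25 SD, so 0.075 SD is 0.3 standard errors. With no true effect, the two-sided error rate becomes Φ(−1.66) + Φ(−2.26), about 6%.

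**4. Exclusion branch: simulation under no true effect (assumed rates).** There were 32 per arm before removal and 20,000 trials per scenario. Worse-scoring participants were more likely to be removed (logit slope 1.5 per SD). The rates shown are for a participant at the mean.

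| Placebo / JDH rate | Bias (JDH − placebo) | Type I error |
|---|---|---|
| 10% / 10% | 0.00 SD | 5.1% |
| 10% / 5% | −0.07 SD | 6.0% |
| 20% / 10% | −0.10 SD | 6.7% |
| 20% / 5% | −0.17 SD | 10.1% |

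Even with outcome-related removal, equal rates in the two arms gave no bias.

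**5. Discontinuation branch.** According to the text of 2.4, SVLT-E is measured at baseline, visit 7 and visit 8. A participant discontinued before visit 7 has only the baseline value. Carried forward, it gives

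- change = baseline − baseline = 0

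The participant stays in the FAS, but with a primary outcome of exactly no change, whatever happened clinically. The other branch would leave the same participant out.

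**6. Effect on power.** At a difference of 0.7 (normal approximation), evaluable numbers of 40, 36, 32, 30 and 28 per arm give power of 87.9%, 84.4%, 80.0%, 77.4% and 74.5%. Power falls below 80% only when fewer than about 32 per arm remain. The removals in step 3 are 5/80 = 6%, against an allowance of 20% (16 of 80).

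**The case against.** The strongest reply is that the two sections can be read together. Section 2.8 plans both an FAS and a PP analysis. If 2.3.2 means exclusion from the PP analysis, there is no conflict. The article also condenses a full protocol, where set definitions and medication lists normally sit. This stands in part: the authors may well have meant PP only. But the sentence in 2.3.2 is unqualified as printed, and the point concerns what it says, not missing detail.

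Several stronger readings are tempting, and the article does not support them:

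- **That affected participants will be dropped and the randomised comparison broken.** Discontinuation is offered as the alternative, and with last-observation-carried-forward it keeps the participant in the FAS. The text creates a risk of exclusion, not a certainty.
- **That the drugs are cognitive drugs taken after worsening.** The article does not list the prohibited drugs. Anti-dementia drugs appear only as an exclusion criterion at entry. A link between use and outcome is plausible but has no source in the article.
- **That the sample shrinks beyond the 20% allowance.** The illustration removes 6%, and these participants may already be counted within the 20%.
- **That the bias favours JDH.** Its direction depends on which arm loses more participants. In the case worked above it runs against JDH.

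The sizes are modest and every rate is assumed, so the point rests on the inconsistency and not on a demonstrated bias.

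**Conclusion.** The point holds in conditional form. Section 2.3.2, taken at its word, permits exclusion from the primary analysis because of a post-randomisation event. That conflicts with the ITT/FAS analysis in 2.8, and nothing in the article resolves it.

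The size of any bias is unknown. It needs drug use that is both related to outcome and unequal between arms. Under assumed rates it ranged from nil to 0.17 SD, with type I error between 5.1% and 10.1%; the simple 4/40 versus 1/40 case gives 0.075 SD. Neither branch is neutral: exclusion selects the analysis set, and discontinuation before visit 7 fixes the primary change at zero. The latter rests on the visit lists in the text of 2.4, which should be confirmed against Table 1.

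The two sections should be reconciled before unblinding, because the choice determines who is in the primary analysis of an 80-person trial.

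**What to change.** Replace the whole analysis consequence in 2.3.2. Changing only its second half would leave participants discontinued from the trial yet still attending assessments. For example:

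> All randomised participants and all their collected data remain in the FAS. Use of these drugs during the trial leads to exclusion from the per-protocol set only, decided at a blinded data review before unblinding. Outcome assessments continue as scheduled where the participant agrees, whether or not study product is stopped.

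A matching cross-reference in 2.8 would close the gap.

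Separately, the sponsor should reconcile the wording of *these drugs*, which can mean the prohibited drugs or the accepted prior medication. No view is taken here on which drugs are prohibited or when study product is stopped.

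The cost is a few sentences and continued follow-up of the participants concerned. There is a small downside: the FAS estimate will include the effect of any added medication. The planned PP analysis offers a view without it, but conditions on the same post-randomisation event and should be read as supportive only.

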#### Inclusion criteria

2.3.3

(1)Males and females 45 years and older and less than 85 years old(2)Participants who are diagnosed with mild neurocognitive disorder based on DSM-5 diagnostic criteria(3)Participants with CDR score of 0.5 and GDS (global deterioration scale) score of 2-3(4)Participants with MoCA-K score of 22(5)Participants who have no limitations in activities of daily living (K-IADL score under 0.43)(6)Participants who have a level of education of more than 6 years (more than elementary education level)(7)Participants or authorized surrogates who voluntarily sign the clinical trial consent form

##### Exclusion criteria

2.3.3.1

(1)Patients with Alzheimer disease, vascular dementia, Parkinson disease, Huntington disease, hydrocephalus, and so on.(2)Patients with other general conditions associated with dementia, such as hypothyroidism, vitamin B12 or folate deficiency, niacin deficiency, hyperkalemia, neurosyphilis, human immunodeficiency virus, and so on.(3)Patients with a SGDS (short-form geriatric depression scale) score greater than or equal to 10(4)Patients who have had major psychiatric disorders such as schizophrenia, delusional disorder, bipolar disorder, alcohol or substance abuse disorder, etc. where were diagnosed according to DSM-5 diagnostic criteria(5)Patients who have had other neurologic diseases such as epilepsy, brain injury, stroke, and so on.(6)Patients who have been taking anti-dementia drugs such as acetyl cholinesterase inhibitors or hormones(7)Patients who have gastrointestinal, endocrine, and/or cardiovascular disease not controlled by diet or medication(8)Patients with unstable medical conditions (investigators will judge will these conditions according to the standard work procedure, based on the results of vital signs, clinical pathology, electrocardiogram, chest radiography, etc)(9)Patients with type 2 diabetes or insulin-dependent diabetes mellitus not controlled by hypoglycemic drugs(10)Patients with hypertension as defined by: systolic blood pressure above 160 mm Hg, diastolic blood pressure above 95 mm Hg(11)Patients who have had clinically significant liver disease or have serum aspartate aminotransferase, alanine aminotransferase, and/or gamma-glutamyl transpeptidase values that are more than twice the laboratory test upper limit reference.(12)Patients who have had chronic renal failure or have serum creatinine value that are more than one and a half times the laboratory test upper limit reference(13)Patients who are pregnant, lactating, or not using appropriate methods of contraception(14)Patients who received Korean medicine treatment for mNCD during the month before the start of the trial within a month before the trial(15)Participants who have participated in other interventional clinical trials during the month before the start of the trial(16)Patients who are assessed as ineligible to participate in the trial by the principal investigator for other reasons

### Study procedure

2.4

The participants who provide written consent and meet the inclusion and exclusion criteria will be selected based on results from the demographic information survey, medical history (past, present, family), vital signs (blood pressure, pulse rate, body temperature), physical examination, laboratory tests, and CDR, GDS, K-IADL, MoCA-K, SGDS scores at the screening visit. Eligible participants will be informed via telephone call and will be asked to visit the trial center within 1 week (visit 1). If participants are taking drugs that may affect the trial, a washout period of at least 15 days will be required before trial start. At visit 1, investigator will check the result from the screening period and changes since that period, and subjects will be allocated to the experimental or the control group using a stratified block randomization method. After randomization, the participants will be administered 6000 mg of JDH or placebo product daily for 12 weeks. Both groups will be instructed to consume the tablets orally, 3 times a day before meals. Subsequently, subjects will undergo assessments for primary and secondary endpoints (SVLT-E, RCFT, DST, Calculation, K-CWST, DSC, K-TMT-E, COWAT, K-BNT, MMSE-DS, MoCA-K, PIT-C, EQ-5D, KQOL-AD, cost analysis, CTIS, BPPA, BIA, WED, fNIRS). They will visit the trial center for evaluation of any changes or adverse effects every 2 weeks. Tests and assessments will be performed according to the following schedule: Visit 2 (Blind test); Visit 4 (WED, fNIRS, MoCA-K, PIT-C, EQ-5D, KQOL-AD); Visit 7 (all tests); and Visit 8 (SVLT-E, Cost analysis, MoCA-K, PIT-C, EQ-5D, KQOL-AD). Detailed assessment schedules are outlined in Table 1. A follow up study will be conducted 12 weeks after the conclusion of the trial.

**Table 1 T1:**
[figure not shown]
Schedule of trial visits.

### Intervention

2.5

The shape and appearance of the JDH tablets and the placebo tablets are the same: black-colored herbal tablets. Each tablet is manufactured at a dosage of 100 mg, with shelf-life of 2 years. The manufacturing company (Hanpoong Pharm. Co., Ltd [name]) follows the regulations for good clinical practice, and controls the quality of the products using their own standards and testing methods.

The principle investigator (PI) will purchase the products used for the clinical trial from the company and supply them to the management pharmacist. Before labeling, 20 tablets will be put in 1 package to prevent mixing. 60 packages, which includes 42 packages for 14 days plus 18 packages for spare will be prepared at 2 week intervals according to the visit schedule. At visit 1 and 6, 51 packages which includes 42 packages for 14 days plus 18 packages for spare will be given. The product label for clinical trials will be filled out following the Regulation on Safety of Pharmaceuticals, and so on. All products used in the trial will be recorded, including the amount of the medication, the date of the delivery, and the date of return.

After randomization, the participants will begin taking 20 tablets of JDH or the placebo by mouth, 3 times a day before meals, for 12 weeks.

### Randomization, blinding

2.6

Independent statisticians who are not involved in the trial procedures will generate the random sequence list using an Excel program. A stratified block randomization method will be used for randomized allocation, for which the stratification factors are the trial centers. The randomized code will be kept in opaque sealed envelopes. Randomized code generation and drug blinding will be implemented independent of the data. The pharmaceutical manufacturing company will label the identification code on the products (JDH and placebo) collectively, and hand them to the PI. The PI will let the management pharmacist to be in charge of the products. At the researcher's request, the management pharmacist at the trial center will provide the participants with either JDH or placebo, corresponding to the identification code in a ratio of 1:1. Both the participants and the investigators will be blinded until completion of the trial.

